Raising the accuracy of diagnosis and subtyping is extremely important for P.A. patients. Screening of P.A. is based on the aldosterone to renin ratio (ARR), and people with abnormally elevated ARR should be screened by further oral salt loading or captopril confirmatory tests [13]. P.A. subtyping test is also an essential, although difficult and challenging, step [13]. Adrenal venous sampling (AVS) was now regarded as the gold standard for P.A. subtyping but only performed in limited centers [12, 14]. Our team was experienced in this technique. Recently, we have developed a computed tomography image fusion, coaxial guidewire technique, and fast intraprocedural cortisol testing (CCF) technique, which significantly increased the success rate of AVS to 98% and shortened the whole procedure time [15]. Moreover, we are still committed to exploring a more optimized AVS procedure.

AVS outcome was interpreted by comparing aldosterone levels in the adrenal venal of the dominant and nondominant side, which could be affected by the position change [16]. Before AVS without corticotropin injection, patients were suggested to keep a supine position to avoid aldosterone fluctuation [13, 17]. However, the length of supine time before AVS had no established standard, although authoritative guidelines recommend recumbency times ranging from 1 h to overnight [13, 17]. In previous work, we chose 1–2 h of supine time as the guideline suggested [17]. We observed many problems were caused by excessive supine time, such as patient’s urinary retention and anxiety, while reduced supine time was found to be more friendly for these patients.

The cortisol level of patients is also an important factor affecting the selective index (S.I.) during AVS. A cohort study showed that at least 15 min of rest before blood sampling was enough to minimize the stress effect and guarantee a satisfactory outcome [18]. Thus, we speculate that 15-min supine time is enough to minimize the fluctuation of aldosterone and cortisol fluctuation caused by position change and preoperative stress.

However, evidence of the most optimal supine time before AVS still lacks, which could simultaneously improve patient satisfaction and compromise the success rate. We expect that the shortened supine time will improve patient experience and ensure the success rate at the same time.

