### Trial design

The study was designed as a multi-center, prospective, two-arm, parallel-group, randomized controlled trial. The protocol is reported in line with the Standard Protocol Items: Recommendations for Interventional Trials (SPIRIT) guidelines following the SPIRIT schedule (Fig. 1) and trial flow chart (Fig. 2). The study was registered on ClinicalTrials.gov: 05658705. The fundamental hypothesis is that reduced preoperative supine time did not affect the subtyping efficacy of AVS. Our hypothesis is based on a simple premise: 15-min preoperative supine time is enough to minimize the fluctuation of serum aldosterone and cortisol levels, thus maintaining the accuracy of AVS outcome.

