#### Adrenal vein sampling procedure

On the surgery day, surgeon and nurse will complete the double check, routine medical record, and signature. Patients of the 15-min group will be first sent to the operating room and kept supine before surgery, and femoral vein sheath inserting will be conducted at the end of supine time. During the operation of the 15-min group, the patient of the 2-h group will be sent to the waiting room and kept supine for 2 h. The surgery procedure is the same in both two groups, which were described below.

AVS without corticotropin stimulation was performed by two professional surgeons ([name] and [name]) as previously described [15]. Briefly, a 5-F sheath was placed into the right common femoral vein under the local anesthetic. The left adrenal vein sampling was accomplished in the central adrenal vein by using a 4-F Simon 1 catheter and a 1.8-F microcatheter. The right adrenal vein was carried out by the guidance of coaxial guidewire technique by using a 4-F Simon 1 catheter. Digital subtraction venography helped to confirm the position of the catheters. The regular order of venous sampling was right adrenal vein, IVC, and left adrenal vein. Three milliliters of adrenal venous blood was obtained by intermittent gentle suction. Venous and IVC cortisol levels will be quickly measured by a conventional enhanced chemiluminescence immunoassay (ECLIA; Roche Diagnostics GmbH, Mannheim, Germany).

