#### Strategies to improve adherence to interventions

The investigators will inform the patients of the benefits and precautions of AVS surgery and thus build and maintain trust with patients.

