### Statistical analysis

An independent statistician will complete the statistical analysis of the study result via the SPSS V25.0. Baseline characteristics will be described by descriptive statistics. *x̅* ± *s* will represent continuous variables with the normal distribution, and the *t* test will compare the differences between the two groups. The Mann–Whitney *U* test will be used in continuous variables that were not normally distributed. Categorical variables will be expressed as frequency (%), and the chi-square test will be used to compare the differences between the two groups. Effect estimates will be provided with corresponding 95% confidence intervals, and *P* values ≤ 0.05 will be considered statistically significant. All randomized participants will be included in the analyses, and data will be analyzed in the group where the participants were randomized initially. The experimental group includes the available data from the 15-min supine group, and the control group includes the available data from the 2-h supine group. The principles of intention-to-treat analysis will be used to preserve the unique benefit of randomization, regardless of whether that participant received the allocated intervention. Multiple imputation (MI) using the mice package in R will be applied to analyze the missing data.

Further secondary analyses will include pre-specified subgroup analyses according to age and the two stratification/minimization variables, investigated by introducing the relevant interaction with treatment allocation into the regression model. In addition, to assess the stability of any intervention effect, we will fit a mixed model for the primary outcome at 3 and 6 months, adjusted for baseline measures.

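### Intention-to-treat is the only analysis set named for a no-effect hypothesis, so departures from the assigned rest that make the arms alike would favour the hoped-for result

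*Protocol article*

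**What the plan says.** Under Trial design: "The fundamental hypothesis is that reduced preoperative supine time did not affect the subtyping efficacy of AVS".

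Under Statistical analysis, all randomised participants are included and "data will be analyzed in the group where the participants were randomized initially", "regardless of whether that participant received the allocated intervention". The further analyses named there are subgroup interactions and a mixed model for the primary outcome at 3 and 6 months. None uses the supine time a patient actually had. The decision rule is a difference test, in which P values of 0.05 or less "will be considered statistically significant". Effect estimates with 95% confidence intervals are promised, but no non-inferiority or equivalence margin is stated.

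Under Adrenal vein sampling procedure, the 15-min patient rests in the operating room and "femoral vein sheath inserting will be conducted at the end of supine time". Meanwhile "the patient of the 2-h group will be sent to the waiting room and kept supine for 2 h". Samples are then taken in sequence: right adrenal vein, inferior vena cava, left adrenal vein.

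The Background says of the team's earlier practice: "We observed many problems were caused by excessive supine time", and names urinary retention and anxiety. The adherence section reads: "The investigators will inform the patients of the benefits and precautions of AVS surgery", with the aim of building trust. It does not address keeping to the assigned rest.

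The Termination criteria list patients who do not finish all treatment. A CRF covering the intraoperative course is mentioned under Interventions, without its items.

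**The concern.** Minutes spent supine are the only thing randomised. In a trial that seeks a difference, analysis as randomised is the cautious choice, because departures from assignment usually shrink the effect. Here the hoped-for result is no effect, so the same shrinkage works in favour of the hypothesis. A patient assigned 2 h who gets up partway may have a posture history closer to that of the short-rest arm, yet counts in full as a 2-h patient.

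At stake is the reading of a null result. It could mean that 15 min is enough, or that the arms were not kept different. Separating the two needs the supine time received and an analysis that uses it, and the article describes neither. It also leaves unclear whether a patient whose rest is broken is terminated or analysed as randomised.

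**Working it through.** **Direction.** Let the true remission rate be p₂ after a full 2-h rest and p₁₅ after the short rest. Let q be the share of the 2-h arm whose rest is broken so that they respond like the short-rest arm. The expected rate in the 2-h arm as randomised is p₂ − q(p₂ − p₁₅), so the expected difference is (1 − q)(p₂ − p₁₅). It moves towards zero for any q above 0.

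**Inputs.** From the article: 60 per arm and alpha 0.05. Taken as two-sided, since sidedness is not stated. Assumed, because the article gives no figures: p₂ = 0.85, p₁₅ = 0.70, and q = 0, 0.1, 0.2, 0.3. That a broken rest loses the whole benefit of the longer rest is also assumed.

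**Calculation.** h = 2·arcsin√(0.85 − 0.15q) − 2·arcsin√0.70; power = Φ(h·√(60/2) − 1.96).

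| q | 2-h arm rate | Difference (points) | h | h·√30 | Power |
|---|---|---|---|---|---|
| 0 | 0.850 | 15.0 | 0.364 | 1.993 | 51% |
| 0.1 | 0.835 | 13.5 | 0.323 | 1.767 | 42% |
| 0.2 | 0.820 | 12.0 | 0.283 | 1.550 | 34% |
| 0.3 | 0.805 | 10.5 | 0.245 | 1.339 | 27% |

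**The article's own effect size.** The Sample size section gives 0.5 with 90% power at 60 per group, without saying what kind of effect size it is. Read as a standardised mean difference, two-sided 5% and 90% power need 2 × ((1.960 + 1.282)/0.5)² = 84.1, so 85 per group. The stated 60 is not reproduced; that is a separate matter. At 60 per group, power is Φ(0.5(1 − q)·√30 − 1.96). This gives 78% for q = 0, then 69%, 59% and 48% for q = 0.1, 0.2 and 0.3. The direction is the same.

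**If no effect were tested as non-inferiority.** The article sets no margin, so assume rates of 90% v 80% and a margin equal to that 10-point loss, so that non-inferiority is false. With one-sided 2.5% and 60 per arm, the chance of wrongly claiming it is Φ((0.10 − Δ)/SE − 1.96), where Δ = 0.10(1 − q) and SE is the unpooled standard error. It is 2.5% for q = 0, then 3.5%, 4.9% and 6.5% for q = 0.1, 0.2 and 0.3.

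**Sampling time.** If cannulation takes t minutes, supine time at sampling is 15 + t or 120 + t. The gap is (120 + t) − (15 + t) = 105 min whatever t is, provided t is alike in both arms.

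**Two passages side by side.** The Termination criteria cover patients who do not complete all treatment. The Statistical analysis section includes all randomised participants whether or not they received their allocation. A patient who abandons the 2-h rest could fall under both, and the article does not say which governs.

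**The case against.** Intention-to-treat is not an error. It answers which resting policy to adopt, and it should stay. What it lacks here is a companion analysis, because its usual caution does not carry over to a no-effect hypothesis.

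Four stronger readings are tempting, and the documents do not support them.

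- *Supine time is not captured, so the trial will hold no data on it.* The article only fails to describe such recording. The CRF covers the intraoperative course and its items are not shown; times of this kind may well be on it. A supportive analysis set may likewise be in a statistical analysis plan that is not at hand.
- *Long rests will be broken.* Urinary retention and anxiety are reported, not patients getting up. Retention while lying down is compatible with staying supine, and nothing says that transfer from the waiting room is upright. Breaks are plausible, not documented.
- *Slow cannulation makes the arms alike.* The procedure is stated to be the same in both arms, so the 105-min gap remains. The contrast in effect would narrow only if the response to posture levels off with time, and the article gives no data on that.
- *The 15-min label is misleading.* The article calls the factor preoperative supine time and says openly that it ends at sheath insertion. Reporting minutes at sampling would add clarity; their absence is not a misstatement.

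It is also fair to object that every rate above is assumed and that total loss of benefit after any break is the extreme case. The 51% power with no breaks at all reflects sample size under those rates, not adherence. These points limit the size of the bias. They leave its direction unchanged.

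**Conclusion.** The point holds in a limited form. For a hypothesis of no effect, the article relies on one analysis set in which loss of contrast between the arms favours the expected answer, and it describes neither an adherence measure for the randomised factor nor an analysis that uses one. The direction follows from the design, given that departures make the arms alike. The size cannot be determined from the article: a loss of 1.5 to 4.5 points from a 15-point difference rests on assumed remission rates, assumed break rates of 10% to 30%, and full loss of benefit after a break. Partial loss would give less.

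The conflict between the Termination criteria and the Statistical analysis section stands on the text alone and needs no assumption. The change is worth making, because a null result is what the trial hopes to report.

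**What to change.** 1. Keep intention-to-treat as it is.
2. Confirm that the CRF records, or add to it: the time supine began, any break in the rest, the mode of transfer to the operating room, the time of sheath insertion, and the time of each adrenal and caval sample.
3. Pre-specify a supportive adherent-set analysis beside intention-to-treat, with adherence defined as the assigned rest unbroken within a tolerance stated in advance. Judge both on the 95% confidence interval for the difference in remission, read against a largest acceptable loss fixed beforehand. Two non-significant P values would show nothing, and the smaller set is the likelier of the two to be non-significant.
4. Report actual supine minutes at sampling by arm, and state that the assigned time ends at sheath insertion.
5. Reconcile the Termination criteria with the Statistical analysis section, so that it is clear how a patient with a broken or abandoned rest is followed and analysed.

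The cost is a few CRF fields and one extra analysis, with no added patients or procedures. The time stamps need to be in place while patients are being sampled, since they cannot be reliably reconstructed later. The downside is that the adherent set is smaller and not fully protected by randomisation, so it can only support the main analysis. The loss of precision would be modest. With 20% of 2-h rests broken, 48 patients remain in that arm, and at the assumed rates the half-width of the interval is 1.96 × √(0.85 × 0.15/48 + 0.70 × 0.30/60) = 15.4 points. With all 60 it is 1.96 × √(0.85 × 0.15/60 + 0.70 × 0.30/60) = 14.7 points.

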### Oversight and monitoring

#### Coordinating center and trial management committee

There are 3 centers that participated in the study: the Second Affiliated Hospital of Zhejiang University of Medicine (initiation center), the First People’s Hospital of Jiashan (participating center), and the First People’s Hospital of Yuhang District of Hangzhou (participating center). The management committee consisted of chief investigator, principal investigators of each workstream, statisticians, and so on and will monitor the process of recruitment, study management, and implementation interventions.

#### Adverse event reporting and harms

This study identifies adverse events including adrenal venous hemorrhage and related adrenal insufficiency, hypertensive urgencies, anaphylactic shock, venous thrombosis, and pulmonary embolism. We will report adverse events to the DMC (Data Monitoring Committee) within 24 h. The reporting will include details on severity, occurrence time, duration, actions taken, outcomes, and causality assessment.

#### Trial conduct auditing

All participating members including doctors, nurses, and analysts will be trained to get acquainted with the whole procedure of this study. Regular online meetings will be held weekly to address difficulties. An independent DMC will be instituted to oversee trial data and adverse reactions and provide suggestions. Monthly meetings will be convened to monitor the trial progress, safety problems, and data quality.

#### Protocol amendments

The principal investigator will be responsible for all protocol modifications. Any updated protocols will be promptly reported to the Chinese Clinical Trial Registry, Clinical Trials, institutional review board (IRB), and all other trial participants.

#### Dissemination plans

The public will not directly participate in this study. The data will not be released directly to the public. The protocol of this study will be publicly available, and the results will be authored and published in academic journals.

## Discussion

P.A. is commonly discovered among patients with resistant hypertension, with a higher risk for earlier cardiac disease, peripheral arterial disease, stroke, and renal injury [20]. With the advancement of diagnosis and subtyping method, P.A. is gradually getting attention from medical staff [21]. However, many controversies remain about the subtyping diagnosis and subsequent treatment of P.A.

C.T. imaging or MRI had limited diagnostic power in P.A. subtyping. AVS is now regarded as an essential standard tool for screening unilateral primary aldosteronism, due to its high efficacy in distinguishing no functional incidentalomas from aldosterone-producing adenomas [13]. The Endocrine Society recommends that all patients with hypertension suspected as primary aldosteronism should accept AVS examination [13]. However, there are many difficulties in performing AVS and interpreting the outcome, and only a few centers can and are willing to carry out this examination. One of the reasons is that surgical protocols of AVS are very different between medical centers, making it hard to standardize the AVS procedure and thus affect the success rate. On the other hand, the patient’s feelings were lack of attention during the whole procedure, which is also an important part of medical quality.

The outcome of AVS, including the selective index (S.I.) and lateralization index (L.I.), are calculated by the serum cortisol and aldosterone levels sampled in the adrenal and inferior veins. In the recent guideline, the European Society of Hypertension recommended S.I. > 2 to demonstrate correct cannulation, and L.I. > 4 to identify the unilateral P.A [22]. Thus, the fluctuation of cortisol and aldosterone is disastrous for interpreting AVS results [23]. Investigators have raised several approaches to avoid the deviation, including corticotropin application and long-time enforced recumbency [17], although there is still a lack of a standardized protocol for AVS.

In this study, we planned to pay attention to the supine time before AVS, which was currently an underappreciated part of the AVS procedure. In current clinical guidelines, the preoperative supine time was set to range from 1 h to overnight [13, 17]. Indeed, long-time supine time, in terms of result, reduced aldosterone fluctuations caused by position change and increased the accuracy of AVS results [16]. However, we should be aware that some patients will feel intense or anxious with time prolonging which may affect the cortisol level and that excessive time reduces the efficiency of surgery [18, 24]. Thus, preoperative supine is important to guarantee a satisfactory outcome of AVS, but the time length of the supine position should be reduced to take care of the patient's feelings.

Our study is the first clinical trial focused on the preoperative lying time of AVS. One limitation of this trial is that it is a multi-center study carried out only in centers in China. Given the differences in the management and success rate of AVS between different centers, this may affect the generalizability of this research. Another limitation of this study is that the patients and investigators cannot be blinded due to the type of study. To minimize the potential influence of this limitation, we will assign the most professional vascular doctor to perform the same operation on the two groups of patients, and the final statisticians will be blind.

In summary, this study will compare the effect of preoperative long-term supine to short-term supine on the outcome of AVS, thereby optimizing effective AVS surgery procedure which would satisfy both the patients and physicians.

## Trial status

This protocol is registered at ClinicalTrials.gov under the number NCT05658705 and it was first posted on 12/21/2022 and last updated on 27/08/2023, https://www.clinicaltrials.gov/ct2/show/NCT05658705. Recruitment will take place from 03/01/2023 to 03/01/2025.

## Data Availability

Not applicable.

## Abbreviations

P.A.: Primary aldosteronism
AVS: Adrenal venous sampling
BMI: Body mass index
SPIRIT: Standard Protocol Items: Recommendations for Interventional Trials
MRA: Mineralocorticoid receptor antagonist
